### Randomization and blinding

To avoid any risk of contamination between the SDM and control groups, cluster randomization will be implemented in this trial. The intervention provided to patients with AF will be grouped by clinicians in a single community health service center. Computer-generated randomization will be used to allocate the intervention and control groups in a 1:1 ratio following AF confirmation. The allocation results of each community health center will be told to the administrators by telephone. Each administrator only knows the result of his or her own site. The researchers, participants, and data analysts will not be blinded, but the participants will not be allowed to know the outcomes of this study.

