### Follow-up

In this study, each patient enrolled will be monitored for at least 2 years, regardless of whether they meet the study’s endpoint or not. For both the SDM group and the control group, the same set of questionnaires will be used for consistency in recording follow-up data. The enrolled patients will undergo follow-ups on the 1st, 3rd, 6th, 12th, 18th, and 24th months through outpatient clinic visits. The follow-up plan will be automatically arranged using the SDM tool. Patient anticoagulation therapy will be re-evaluated based on follow-up data, and information on patients’ records and past data will be retrieved from the SDM tool’s cloud platform. At each follow-up time point, patients in the SDM group will complete the questionnaires within the tool, while patients in the control group will complete the questionnaires within the clinical case report form (CRF). A designated medical staff member will send text reminders to patients to attend follow-ups. Patients in the control group who cannot attend scheduled follow-ups at the community health service centers can be followed up by telephone.

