### Sample size

This multicenter, cluster-randomized clinical trial aims to evaluate the occurrence of bleeding events as the primary outcome. The anticoagulation bleeding rate of patients with AF in our hospital was previously found to be 20% [24], and an effective intervention reduces the incidence of bleeding by 15% [35]. We set the power at 80% with a bilateral two-tailed significance of 5%. To achieve a sample size of 88 cases in both the intervention and control groups, with a 20% loss to follow-up rate, we estimated a minimum of 110 cases in each group. However, taking the clustering into account, we increased the sample size to account for the design effect to achieve the required statistical power under cluster randomization. Therefore, using the bleeding rate as the calculating target and a design effect of 2, we estimated a sample size of 440, which was calculated using the PASS software version 15.

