### Statistical analyses

In accordance with standard practice, continuous variables will be presented as means ± standard deviation, while categorical variables will be expressed as proportions. The Kolmogorov–Smirnov test will be utilized to determine the normality of the data. Student’s *t*-test or Mann–Whitney’s *U*-test will be applied to compare two groups, depending on the distribution of the data. For categorical data, comparisons between the groups will be performed using the chi-square or Fisher’s exact tests. Time in therapeutic range (TTR) will be evaluated for patients on warfarin. Multiple imputations will be used to fill in missing values, and both per-protocol (PP) analysis and intention-to-treat (ITT) analysis will be conducted. Subgroup analyses will be performed based on patients’ age groups, treating hospitals, liver or kidney function, the type of anticoagulants used, etc. Statistical significance will be assumed for *p* values less than 0.05. All statistical analyses will be conducted with the IBM SPSS version 22.0 software.

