#### Composition of the Data Monitoring Committee, its role, and reporting structure

This study has no composition of Data Monitoring Committee (DMC) as this is a low-risk intervention, and other data will be reserved in the information security department as parts of patients’ medical records.

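### The plan states without a reason that the data analysts will not be blinded, although coding arm and centre for the primary analysis would cost little

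*Protocol article*

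**What the plan says.** The Randomization and blinding section settles the matter in one clause: "The researchers, participants, and data analysts will not be blinded". It gives no reason for including the analysts. The same section does limit knowledge of allocation elsewhere: each centre's administrator learns only that centre's result.

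No other section of the article provides for coded arm labels, a masked data review or a separate key holder. On oversight, the article says: "This study has no composition of Data Monitoring Committee (DMC) as this is a low-risk intervention". It also reports that no additional steering committee was considered. The clinical research unit monitors conduct and data traceability (Monitoring), but masked analysis is not among its listed tasks.

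The Statistical analyses section describes the work of these analysts. Missing values are to be multiply imputed, and "both per-protocol (PP) analysis and intention-to-treat (ITT) analysis will be conducted". For continuous outcomes, a t-test or "Mann–Whitney’s *U*-test will be applied to compare two groups, depending on the distribution of the data". For categorical outcomes, which include the primary bleeding outcome, "comparisons between the groups will be performed using the chi-square or Fisher’s exact tests". Subgroups are to be formed by age group and by "treating hospitals, liver or kidney function, the type of anticoagulants used, etc".

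**The concern.** Some openness is unavoidable here. A clinician who prescribes with the tool, and a patient who answers questionnaires inside it, know their arm. An analyst is in a different position. A comparison of two groups needs two labels, and the meaning of the labels is not needed until the result is interpreted.

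Several steps in the analysis involve judgement: who counts as per-protocol, which variables enter the imputation model, and which subgroups are added to a list that is left open. An analyst who knows the arms can see, even without intending to use it, which choice helps the tool. The Background says that the team running the trial also developed the tool. That makes a visible separation between the team and the analytic choices more useful when the result is read by others.

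At stake is how far readers can trust those choices. Patient safety and sample size are not affected.

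**Working it through.** **1. The plan's own figure, and whether it is affected.** Inputs from the Sample size section: 20% bleeding under usual care, a reduction of 15 (read as percentage points, so 5% under the tool), power 80%, two-sided 5%, 20% loss to follow-up and a design effect of 2.

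- Uncorrected n per group = [1.960·√(2·0.125·0.875) + 0.842·√(0.20·0.80 + 0.05·0.95)]² / 0.15² = 75.1, so 76.
- With continuity correction: (75.1/4)·[1 + √(1 + 4/(75.1·0.15))]² = 87.9, so 88.
- Loss to follow-up: 88/0.80 = 110 per group.
- Clustering: 110 × 2 groups × 2 = 440.

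The stated 88, 110 and 440 are reproduced. None of the inputs concerns who knows the allocation, so masking the analysts leaves 440 unchanged.

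**2. Who needs to know the arm.**

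| Role | What the article has them do | Needs the arm? |
|---|---|---|
| Clinicians, pharmacists | Prescribe and educate with the tool, or give usual care (Interventions) | Yes |
| Patients | Answer questionnaires in the tool or on the case report form (Follow-up) | Cannot be masked |
| Researchers reporting serious events | Report to the ethics committee; attribution to the tool matters (Data collection and management) | Yes |
| Data analysts | Tests, imputation, analysis sets, subgroups (Statistical analyses) | Only as two codes |

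**3. Which analytic choices are open.**

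- *t-test or rank test:* governed by a normality test, and not relevant to the binary primary outcome. Little room.
- *Chi-square or Fisher:* no rule is given, but the two differ little at about 220 per arm and 20% events. Little room.
- *Multiple imputation:* the method is named, the model is not described. Some room.
- *Per-protocol and intention-to-treat:* both will be run. Neither is named as primary, and per-protocol membership is not defined in the article. Some room.
- *Subgroups:* the list is open-ended. Some room.

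Knowledge of the arm can therefore matter for three items: the analysis set, the imputation model and the subgroups.

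**4. What could reveal the arm to a masked analyst.**

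- Treating hospital is a planned subgroup and is also the unit of randomization, so a centre's name discloses its arm. Coded centres hide this and still show which patients belong to the same cluster.
- Questionnaires come from the tool in one arm and from the case report form in the other. Telephone follow-up is stated only for controls. Source and contact-mode fields would have to be removed, and differing patterns of missing data might still hint at the arm.
- A per-protocol criterion based on use of the tool applies to one arm only, so a masked analyst cannot apply it.

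Each of these can be handled by someone who holds the key and does not carry out the analysis.

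**The case against.** The strongest reply is that the article condenses a fuller protocol. A statistical analysis plan that is not shown may fix the imputation model, the per-protocol definition and the subgroups before any data are seen, and little would then be left for an unmasked analyst to influence. This stands in part. Full pre-specification would shrink the consequence, and the absence of those details from an article is not a fault. But the unblinding itself is stated outright, so it is not a detail left for later.

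Other points also stand. Test selection leaves little room. Multiple imputation and both analysis sets are already committed to. Masking would take some work and might be incomplete.

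A reader might infer more than the documents support, in three ways.

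- *That unblinding raises the false-positive rate by a calculable amount.* One can simulate null trials with 220 independent patients per arm, 12.5% or 20% bleeding, and an assumed per-protocol set of 60 to 80% of patients. Reporting the smaller of the two p-values then gives about 7 to 8% instead of 5%. But a two-sided p-value is the same when the arms are swapped, so an analyst who sees only A and B could pick the same minimum. The figure measures missing pre-specification, not lack of masking. It also rests on invented per-protocol fractions and ignores clustering. Nor does multiple imputation, done as named, add inflation: pooling five imputed sets by Rubin's rules kept the error at about 5% (176 of 220 observed per arm, 20% bleeding).
- *That masking is free, or the only safeguard left.* The two data routes mean it is not free. Masked adjudication of bleeding would be another safeguard. It addresses the recording of minor bleeds in an open trial, which analyst masking does not.
- *That the sponsor intends to steer the result.* Nothing in the document suggests this.

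**Conclusion.** The point holds as a modest one. The protocol chooses to leave the analysts unblinded, gives no reason, and assigns them no task in the primary analysis that requires the meaning of the arm labels. In an open trial without a data monitoring committee, analyst masking is one inexpensive safeguard that the plan gives up. The exposure is confined mainly to per-protocol membership, the imputation model and the choice of subgroups.

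Its size cannot be stated as a number from these documents. The conclusion assumes that the unseen plan does not already separate the analysts from the arm key, and a plan consistent with the sentence as written would not. If that plan fixes the three open choices in advance, the remaining benefit of masking is smaller, but it still covers case-by-case calls on per-protocol membership.

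**What to change.** Amend the sentence in Randomization and blinding to say that researchers and participants will not be blinded, but that the primary analysis will be done on data with arm and centre coded. In detail:

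1. Someone outside the analysis, for example existing clinical research unit or data-management personnel, merges the tool and case-report-form data, replaces arm and centre by codes, removes source and contact-mode fields, and holds the key.
2. The key is released only after per-protocol membership, the imputation model and the primary analysis code have been locked and run.
3. Any per-protocol criterion that depends on use of the tool is applied by the key holder under a rule written beforehand.
4. The subgroup analysis by treating hospital uses coded centres or follows unmasking.

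If the team considers masking unworkable, the protocol should state why.

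The cost is a small protocol change and a small amount of data-management work. Care, follow-up, safety reporting and the sample size of 440 are unchanged, and the step can be introduced at any time before the data set is handed over for analysis. Because the data sources differ by arm, masking may be imperfect, and the report should say so.

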### Interventions

#### Introduction

Community health service centers that are randomized to the SDM group will utilize the SDM tool to manage AF patients. The medical specialists involved in this study will have access to the SDM tool. The anticoagulation regimens for AF patients will be determined through communication between the clinicians and patients based on the suggestions and information provided by the SDM tool. This includes anticoagulation strategies that have a corresponding net clinical benefit (NCB), cost of each anticoagulant, blood examination of warfarin, and other relevant considerations. Clinicians will prescribe dosage regimens and order appropriate laboratory monitoring based on the recommendations of the SDM tool. Furthermore, this SDM tool can also assist clinicians with anticoagulation regimes in AF patients with specific circumstances, such as adjuvant bridging therapy, periprocedural anticoagulation recommendations, and drug regimen adjustments for end-organ function, weight, and concomitant interactions. With the help of the SDM tool, pharmacists can provide comprehensive patient education, including indications for the therapy, medication intake, medication interactions, laboratory monitoring, activity, diet, side effects, pregnancy, procedures, safety precautions, and self-care. The SDM tool will also enable the tracking of bleeding and other adverse events relevant to anticoagulation, as well as assessing patients’ knowledge, adherence, and satisfaction with anticoagulation therapy. The tool will automatically schedule the follow-up scheme, and the anticoagulation therapy will be reassessed based on the follow-up data of the patients. The records and information of the patients will be obtained from the SDM tool cloud platform. In contrast, the control group will receive the usual care based on the clinicians’ usual approach.

#### Introduction of the anticoagulation SDM tool (I-Anticoagulation)

In a previous study, a novel anticoagulation shared decision-making (SDM) tool was developed with the input of healthcare professionals including physicians, pharmacists, and nurses [24]. To facilitate optimal anticoagulation management, a WeChat Mini application-based tool called I-Anticoagulation was created, which offers a flexible and efficient communication platform for healthcare professionals and AF patients. The tool is composed of two modules: an anticoagulation decision support system and a full-process patient management system.

The anticoagulation decision support system requires the input and recording of baseline information of patients with AF, such as age, weight, gender, smoking, alcohol consumption, diagnosis, complications, comedications, history of stroke and bleeding, blood pressure, liver and kidney function, and heart function [24]. Liver function will be assessed using the Child–Pugh score, and renal function will be calculated using the Cockcroft-Gault formula based on creatinine clearance. The tool can automatically calculate CHA2DS2-VASc and HAS-BLED scores to evaluate the patient’s stroke and bleeding risks, respectively, based on incidence data for Asian AF patients [26–28]. The anticoagulation strategies with NCB values will also be presented on I-Anticoagulation.

Patients on anticoagulant therapy can be enrolled in the full follow-up management system, with patient information updated at each follow-up visit, including adjusted dose, INR value (if warfarin was used), the reason for unstable INR, thromboembolic/bleeding events during anticoagulation, and other changing characteristics. The risks of stroke and bleeding will be dynamically reassessed according to the changes in patient characteristics, and the NCB for each anticoagulant drug will also be recalculated, with dynamic recommendations for appropriate anticoagulation regimens.

In addition, the SDM tool includes a series of questionnaires, such as the Anticoagulation Knowledge Tool (AKT) [29], Medication Adherence Reporting Scale (MARS-5) [30], and Anti-Clot Treatment Scale (ACTS) [31], to evaluate medication knowledge, adherence, and satisfaction of AF patients receiving anticoagulation.

Clinicians can search for recommended anticoagulation strategies based on the latest guidelines or consensus for patients with AF affected by renal/liver impairment, coronary artery disease (CAD), perioperative period, or switching to a different type of anticoagulant.

### Follow-up

In this study, each patient enrolled will be monitored for at least 2 years, regardless of whether they meet the study’s endpoint or not. For both the SDM group and the control group, the same set of questionnaires will be used for consistency in recording follow-up data. The enrolled patients will undergo follow-ups on the 1st, 3rd, 6th, 12th, 18th, and 24th months through outpatient clinic visits. The follow-up plan will be automatically arranged using the SDM tool. Patient anticoagulation therapy will be re-evaluated based on follow-up data, and information on patients’ records and past data will be retrieved from the SDM tool’s cloud platform. At each follow-up time point, patients in the SDM group will complete the questionnaires within the tool, while patients in the control group will complete the questionnaires within the clinical case report form (CRF). A designated medical staff member will send text reminders to patients to attend follow-ups. Patients in the control group who cannot attend scheduled follow-ups at the community health service centers can be followed up by telephone.

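### Knowledge, adherence and satisfaction are scored inside the intervention tool in the SDM arm and on a case report form in the control arm, so mode of administration is fully confounded with arm for these secondary outcomes

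*Protocol article*

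**What the plan says.** All references are to the protocol article.

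- **Follow-up** promises common instruments: "the same set of questionnaires will be used for consistency in recording follow-up data". Timing is also common: "The enrolled patients will undergo follow-ups on the 1st, 3rd, 6th, 12th, 18th, and 24th months through outpatient clinic visits". Table 3 marks the three questionnaires at day 0 as well.
- **Follow-up** then splits the mode by arm at each follow-up point: "patients in the SDM group will complete the questionnaires within the tool", whereas controls answer in the case report form. Telephone follow-up for missed visits is stated for control patients only.
- **Introduction of the anticoagulation SDM tool** makes the questionnaires part of the product: "the SDM tool includes a series of questionnaires", naming AKT, MARS-5 and ACTS.
- **Interventions, Introduction** lists among the tool's functions the tracking of events "as well as assessing patients’ knowledge, adherence, and satisfaction with anticoagulation therapy". The same paragraph says: "With the help of the SDM tool, pharmacists can provide comprehensive patient education".
- **Randomization and blinding** leaves researchers, participants and analysts unblinded.
- **Secondary outcomes** includes knowledge, adherence and satisfaction, measured by these three instruments. The **Background** also names adherence and satisfaction in the study aim.
- **Statistical analyses** compares continuous data between the two groups by t-test or Mann–Whitney test.

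**The concern.** The three scores are self-reports from patients who know their arm. In one arm they are entered into the application that delivers the intervention; in the other they are entered on a research form. At follow-up no SDM patient is assigned the research form and no control patient the tool. An effect of mode or setting on how people answer would therefore appear as a difference between arms, and the two-group comparison would report it as an effect of the tool.

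Adjustment cannot repair this. The main mode does not vary within either arm, so a mode term would be the arm term under another name. Only a change in collection separates the two.

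At stake is the reading of three secondary outcomes, two of which (adherence and satisfaction) also stand in the study aim.

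**Working it through.** **1. Setting the arms side by side**

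| Feature | SDM arm | Control arm |
|---|---|---|
| Instruments | AKT, MARS-5, ACTS | the same |
| Follow-up schedule | months 1, 3, 6, 12, 18, 24 | the same |
| Mode at follow-up | inside I-Anticoagulation | case report form |
| Telephone follow-up for missed visits | not stated | stated |
| Questionnaires part of the treatment | yes | no |
| Participant blinded | no | no |

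Repeated testing is common to both arms and cannot explain a difference. Mode and setting differ completely by arm.

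**2. The plan's own figures, to fix the number of patients**

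The Sample size section gives 88 per group, 110 after loss, and 440 in total.

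- 20% versus 5%, two-sided 5%, 80% power, with continuity correction: 88 per group.
- 88 / (1 − 0.20) = 110 per group.
- 110 × 2 groups × design effect 2 = 440, or 220 per arm.
- Evaluable after 20% loss: 220 × 0.80 = 176 per arm.

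These figures reproduce. They concern bleeding and serve here only to supply 176 per arm, 8 centres and design effect 2.

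**3. What a pure mode shift would do**

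The protocol gives no size for a mode effect. Assume a shift d of 0.1, 0.2 or 0.3 SD between modes and no true benefit.

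*Patient-level test, no centre effect.* SE = √(2/176) = 0.107 SD. The chance of p<0.05 is Φ(d/SE − 1.96) + Φ(−d/SE − 1.96).

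*Centre-level test, design effect 2.* SE = √(2 × 2/176) = 0.151 SD. With 8 centres there are 8 − 2 = 6 degrees of freedom and a critical value of 2.447. The chance comes from a noncentral t with noncentrality d/SE.

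| Assumed shift | d/SE, patient level | P(p<0.05), patient level | d/SE, centre level | P(p<0.05), centre level |
|---|---|---|---|---|
| 0.1 SD | 0.94 | 0.155 | 0.66 | 0.087 |
| 0.2 SD | 1.88 | 0.467 | 1.33 | 0.202 |
| 0.3 SD | 2.81 | 0.804 | 1.99 | 0.388 |

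A normal test with 88 effective patients per arm (176 / 2) falls between: 0.10, 0.26 and 0.51.

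The centre-level column isolates the mode problem. The patient-level column shows the type of comparison that the Statistical analyses section describes, with no clustering present.

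**The case against.** The best reply is that the plan already standardises what matters: the same instruments, at the same times, in both arms. That stands, and it removes repeated testing as an explanation. It does not remove mode or setting.

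A reader might infer a stronger charge, that the scores are biased in the tool's favour. The documents do not support this:

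- **Teaching to the test.** Nothing says that the tool returns AKT answers or scores to patients. Knowledge gained from tool-supported education is an intended effect, not an artefact.
- **Answering to one's own clinician.** Therapy is re-evaluated from follow-up data, but questionnaire answers are not named among the information updated at visits. Nor does the text say that control forms are hidden from clinicians. Different visibility is not shown.
- **Baseline taken in the tool.** The in-tool rule is stated for follow-up points. Table 3 marks day 0 without giving a mode.
- **Direction.** If control patients answer by telephone to staff, their reports could be inflated, which would work against the tool.

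The illustration is also open to challenge. The shifts are assumptions. The three outcomes concern patients receiving anticoagulation, so fewer than 176 per arm may contribute, and that would lower every percentage. Both points stand; they limit what can be said about size but leave the confounding in place.

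Finally, an article may leave operational detail to the full protocol. Here, though, the article itself fixes a different mode for each arm.

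**Conclusion.** The point holds as confounding of mode and setting with arm for AKT, MARS-5 and ACTS in an unblinded trial. Differences in these scores may partly reflect mode, and no analysis of data collected this way can separate the two. It does not follow that the scores carry no information or that they favour the SDM arm; direction and size are unknown.

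Under assumed shifts of 0.1 to 0.3 SD with no benefit and 176 per arm, false positive rates would run from about 9% to 39% for the centre-level test, against a nominal 5%. For a patient-level test without centre effects they would run from 16% to 80%. These are illustrations, not estimates.

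The primary bleeding outcome is untouched by this point. The change is worth making because it is cheap and removes an avoidable ambiguity, but it is not critical to the trial's main result.

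**What to change.** Amend the Follow-up section as follows.

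- Both arms complete AKT, MARS-5 and ACTS on the same self-completed case report form, outside I-Anticoagulation, at every scheduled time point. The research assistant already planned for each centre hands it out.
- The telephone fallback is the same in both arms, and its use is recorded.
- Only these forms count as trial outcomes. The in-app versions are not given at the same visit, so that SDM patients are not tested twice.
- The day-0 form is completed before the tool is first used.
- For patients already enrolled, the mode is recorded at each visit and a sensitivity analysis limited to common-mode assessments is reported.

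The cost is small. SDM patients answer outside the app and data entry rises a little. The real limit is timing: enrolment began in October 2022, so assessments made before the amendment stay in mixed mode, and the sensitivity analysis will rest on fewer assessments.

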#### Primary outcomes

While thrombotic events are a critical consequence of AF, the incidence rate of these events in patients who are adequately anticoagulated is generally lower than the incidence of bleeding events. Consequently, the study’s primary outcomes comprise any bleeding events, both major and minor. Major bleeding events [32] include fatal hemorrhage, life-threatening bleeding, and severe bleeding requiring treatment or assessment. Severe bleeding can manifest as gastric intestinal hemorrhage, joint hematoma, retroperitoneal hemorrhage, fundus hemorrhage, urine, hemoptysis, or require blood transfusion of at least two units. In contrast, minor bleeding events, such as mild nasal hemorrhage, endoscopic hematuria, skin stasis, or mild hemorrhoids, do not lead to serious consequences [33].

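### Bleeding may be ascertained unequally: the telephone fallback is given to controls only, the SDM tool itself tracks bleeding, and researchers, participants and analysts are unblinded

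*Protocol article*

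**What the plan says.** Under Primary outcomes, "the study’s primary outcomes comprise any bleeding events, both major and minor". The minor category is mild by definition: "minor bleeding events, such as mild nasal hemorrhage, endoscopic hematuria, skin stasis, or mild hemorrhoids, do not lead to serious consequences".

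Three statements make data collection differ by arm:

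- **Missed visits (Follow-up).** "Patients in the control group who cannot attend scheduled follow-ups at the community health service centers can be followed up by telephone". No matching provision is stated for SDM patients.
- **Tracking of bleeding (Interventions, Introduction).** "The SDM tool will also enable the tracking of bleeding and other adverse events relevant to anticoagulation". The section introducing the tool says "Patients on anticoagulant therapy can be enrolled in the full follow-up management system", and lists among the items updated at each visit "thromboembolic/bleeding events during anticoagulation, and other changing characteristics".
- **Recording medium (Follow-up).** At each time point "patients in the SDM group will complete the questionnaires within the tool, while patients in the control group will complete" theirs in the case report form (CRF).

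On masking, Randomization and blinding states: "The researchers, participants, and data analysts will not be blinded".

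Other statements apply to both arms. Follow-up gives them the same set of questionnaires and clinic visits at months 1, 3, 6, 12, 18 and 24. Outcomes sets collection at those same months. Text reminders are not limited to one arm.

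**The concern.** A mild nosebleed, a bruise or slight haemorrhoidal bleeding usually reaches the data only if the patient is asked about it or volunteers it. The recorded rate therefore depends on who is contacted, how and by what means. Here a control patient who misses a visit may be telephoned, while the article gives no such route for an SDM patient. In the SDM arm the system that records bleeding is part of the intervention under test. Patients and staff know the arm when bleeds are reported and recorded, and analysts know it when the data are handled.

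The two differences can act in opposite directions. Tracking by the tool may raise recorded bleeding in the SDM arm and hide a benefit. Telephone contact may recover bleeds among absent controls that would be lost among absent SDM patients, which would exaggerate a benefit; it may also pick up mild bleeds less well than a clinic visit does. At stake is whether a difference, or the lack of one, in the main result can be attributed to the tool.

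**Working it through.** **1. The plan's own figures.** The Sample size section gives 20% bleeding, a reduction of 15%, 80% power, two-sided 5%, 88 per arm, 110 per arm after 20% loss, design effect 2 and 440 in total. Taking the 15% as percentage points (20% to 5%):

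- Uncorrected: n = [1.96·√(2·0.125·0.875) + 0.8416·√(0.20·0.80 + 0.05·0.95)]² / 0.15² = (0.9167 + 0.3834)² / 0.0225 = 75.1, so 76 per arm.
- With continuity correction: (75.1/4)·[1 + √(1 + 4/(75.1·0.15))]² = 87.9, so 88 per arm.
- 88/0.80 = 110, and 110 × 2 arms × 2 = 440.

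The stated figures reproduce. Read as a relative reduction (20% to 17%), the same formula gives 2,695 per arm with the correction, so the percentage-point reading is used below. The sample size is not in dispute here.

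**2. Effective size.** 440 × 0.80 = 352 completers, or 176 per arm. Dividing by the design effect of 2 leaves an effective 88 per arm.

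**3. No true effect, unequal recording.** The documents give no capture rates, so these are assumptions. Let the true rate be 20% in both arms. One arm records every bleed and the other records a share s. With p1 = 0.20, p2 = 0.20·s, d = p1 − p2, p̄ = (p1 + p2)/2 and n = 88:

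- SE0 = √[2·p̄·(1 − p̄)/n]
- SE1 = √[(p1(1 − p1) + p2(1 − p2))/n]
- Chance of a significant result = Φ[(d − 1.96·SE0)/SE1] + Φ[(−d − 1.96·SE0)/SE1]

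Worked for s = 0.80: p2 = 0.16, d = 0.04, p̄ = 0.18, SE0 = 0.0579, SE1 = 0.0578. The two terms are Φ(−1.27) = 0.102 and Φ(−2.65) = 0.004, together 10.6%.

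| Share recorded in one arm (assumed) | Recorded rates | False difference | False-positive rate |
|---|---|---|---|
| 100% | 20% vs 20% | 0 points | 5.0% |
| 90% | 20% vs 18% | 2 points | 6.3% |
| 80% | 20% vs 16% | 4 points | 10.6% |
| 70% | 20% vs 14% | 6 points | 18.4% |

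A shortfall in the SDM arm would look like a benefit; a shortfall in controls would look like harm.

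**4. The planned effect, with controls under-recorded.** With true rates of 20% vs 5% and 88 per arm, power without continuity correction is 85.9% under full capture. It falls to 77.6%, 66.5% and 53.1% if controls record 90%, 80% and 70% of their bleeds.

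**5. Whether the analysis can repair this.** Statistical analyses plans multiple imputation with intention-to-treat and per-protocol analyses. Imputation can address a visit that is visibly missing, provided the absence is explained by observed data. It cannot restore a mild bleed that was never asked about in a patient who attended, because that patient is recorded as having no bleed.

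**The case against.** Much can be said for the plan. What the article fixes for outcomes is common to both arms: questionnaires, visits and time points. Open-label delivery is unavoidable when a patient-facing tool is compared with usual care. Major bleeding, which depends less on prompting, is already a secondary outcome. The source is a condensed article, so a bleeding form or classification procedure may well stand in the full protocol, and its absence here is no fault.

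Four stronger readings are tempting, and the documents do not support them:

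- *Bleeding comes from the tool in one arm and only from the CRF in the other.* The sentence on tool versus CRF concerns questionnaires. Those named are the AKT, MARS-5 and ACTS, which measure knowledge, adherence and satisfaction. The link to bleeding rests on the tool's tracking function. No sentence says how control bleeds are recorded.
- *SDM patients not taking an anticoagulant escape outcome collection.* The wording describes whom a software module can enrol. Follow-up has every enrolled patient monitored for at least 2 years, and Outcomes sets no anticoagulant condition.
- *The tool logs extra bleeds between visits.* The article says only that information is updated at each follow-up visit, on a schedule that controls share.
- *The planned 20% loss shows how many SDM patients would go uncontacted while all controls are reached.* Sample size applies that loss to both arms, and nothing says that telephoning recovers every control.

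The telephone rule survives these objections. It is an express rule for obtaining outcome data in one arm, not a detail left to another document. The common questionnaires and visits do not offset it, because it operates exactly when a visit is missed.

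**Conclusion.** The concern holds in a limited form and is a should-fix. Following the article as written can make recorded bleeding differ by arm without a true difference, because the missed-visit rule and the recording medium differ, the tool under test tracks bleeding, the outcome includes mild self-noticed events, and patients, researchers and analysts are unblinded. The shared schedule and questionnaires reduce this risk without removing it.

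Neither direction nor size can be read from the documents. The range of a 2 to 6 point false difference, with a false-positive rate of about 6% to 18%, rests on an assumed relative shortfall of 10% to 30% in one arm, a true rate of 20% in both, a normal approximation and an effective 88 per arm. It shows what modest inequality would do; it does not estimate what will happen.

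**What to change.** 1. Offer the telephone fallback for missed visits on identical terms in both arms.
2. Ascertain the primary outcome in both arms with one structured set of bleeding questions, put to every enrolled patient at months 1, 3, 6, 12, 18 and 24 whether or not an anticoagulant is taken. Any bleed known only through the tool goes into a sensitivity analysis.
3. Give the analyst coded arm labels until the primary analysis is locked. This protects the analysis stage only; items 1 and 2 are what make reporting comparable.
4. Add a sensitivity analysis restricted to medically attended bleeding, alongside the existing major-bleeding secondary outcome.

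The cost is a few extra calls in the SDM arm, one shared form and coded labels. Bleeds known only through the tool leave the primary analysis. Enrolment began in October 2022, so visits before the change were collected under the old rule and should be flagged in the data. With enrolment expected to run to April 2024 and at least 2 years of follow-up per patient, a change made during the trial can still cover later visits. The sample size and clinical management are unaffected.
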